### Scalability

With scalability central to our vision, all partner solutions are at technology readiness Level 9, with next to zero time to solution required. Our scalability report will include documentation of (1) unforeseen issues as they arise and problem solving strategies, (2) patient and SVN experience, and (3) results of our comprehensive econometrics evaluation plan, distilled into a projected model of total cost of 1-year SMArTVIEW patient throughput, based on site surgical volumes.

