#### Feasibility

Our technology partners have contributed equipment and personnel time, in-kind, such that we are able to intervene and follow up on 15 patients at one time per site throughout the study until 30 days follow-up, at which time equipment will be returned to each hospital site for cleaning and reset. Therefore, the RCT (Phase 2) will be executed in five serial, parallel waves of approximately 30 patients per site. In 2014, there were 2311 and 1974 CaVS performed at Hamilton Health Sciences, Canada, and the Liverpool Heart and Chest Hospital, the United Kingdom, respectively. Planned recruitment will occur at a rate feasible for SVN time and access to the surgical populations at both sites. Patients will be enrolled during a 3-week period, with the last week of each recruitment month available for additional patient registrations as needed to accommodate those not meeting postop eligibility. Each site will target recruitment of 14 cardiac and 16 vascular patients during 3 weeks of recruitment—10 patients per week, per site. Allowing for a 25% refusal rate, lost opportunities, and competing studies, this still provides access to 20 patients at Hamilton Health Sciences and 17 patients at the Liverpool Heart and Chest Hospital. Since participant recruitment is only limited by prototype availability, our proposed recruitment target and timeline is feasible and recruitment of 300 participants will be completed in 10 months’ time.

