### Data Analyses

#### Primary Analyses

Table 3 summarizes all data analyses. Using the intent-to-treat principle [128], all patients will be included in the final analysis and according to the group to which they were randomly allocated. Descriptive statistics will be used to describe sample characteristics using measures of central tendency and dispersion for continuous factors, and frequencies and proportions for categorical factors. A two-sided significance level of .05 will be used for all inferential analyses. Statistical methods used will depend on the type and distribution of data for the outcome variable under study. If outcome data meet requirements for parametric statistics, a linear mixed model [129] will be used to assess the effects of the intervention on the primary outcome. An a priori contrast of the weekly average worst score for the BPI-SF numeric rating scale *upon movement* (previous 24 hours) will be used to evaluate the primary endpoint of acute postop pain at 30 days postrandomization.

Linear mixed models, using an autoregressive [130] covariance structure—allowing for correlations between measurements to decline as they are further apart in time—will be used to evaluate within-patient variation in patient-reported outcomes over 12 months of follow-up. Linear mixed models are a flexible and powerful approach to the analysis of data with a complex variance structure, such as correlated data [129-131]. Unlike traditional repeated-measures designs, these models do not require complete data on each patient and have increased statistical power [132]. Nonlinear mixed models will be used in the following cases: (1) if continuous data violate assumptions of normality [132] and (2) for categorical secondary outcomes (eg, adverse event). Chi-square tests of association will be used to assess the association between categorical secondary outcomes identified in the administrative data and intervention. Given that the data is derived from an RCT, complex modeling for these outcomes will not be performed, as potential confounders are considered to be adjusted for in the design. Finally, we will examine patterns of missing data and determine demographic and/or clinical characteristics that are related to missing data at each time point, and the potential impact on the primary findings.

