#### Subgroup Analyses

Two types of separate subgroup analyses are planned to determine the impact of gender-based pain expectations and patient sex on intervention effectiveness (see Table 3):

1. Patients will be stratified into high versus low GREP scores. The primary analyses examining the effect of the intervention on the worst score for the BPI-SF numeric rating scale *upon movement* (previous 24 hours) will be conducted. An interaction term for GREP score (low versus high) and the group allocation will be incorporated into the analyses to determine if gender-based pain expectations are associated with differences in the effect of the intervention on the primary outcome. If a significant interaction is identified, the primary analysis in these two groups will be performed.

2. Similarly, interaction between the intervention and patient sex will be examined.

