#### Cost-Effectiveness Analyses

The cost-effectiveness of implementing the intervention will be determined from two perspectives: (1) the Ministry of Health and Long-Term Care (MoHLTC) (Canada) and (2) society (Canada and the United Kingdom) (see Table 3). Separate analyses will be conducted from each perspective. MoHLTC costs will include costs associated with health service utilization over the study period (eg, hospitalization, emergency room visits, day surgery or procedure, laboratory services, outpatient visits, prescription drugs, and home care services from the Institute of Clinical Evaluative Sciences). Time that health providers (eg, pharmacists) spent on the SMArTVIEW portal will be calculated by multiplying the time with unit costs from standard costing sources in Ontario. From the societal perspective, costs will include those from the MoHLTC perspective, including costs incurred to patients and family members (eg, travel cost and productivity loss), which will be captured through the AHCR.

The first economic analysis outcome is the incremental cost of the intervention compared to usual care. We will analyze the total cost as a dependent variable, using a regression model to estimate the difference in expected health care cost between the two groups. The intervention will be the primary independent variable and the regression model will adjust for potential confounding variables. In theory, an ordinary least squares model produces unbiased estimates even if the data are skewed [135,136]; however, additional estimation methods (eg, generalized linear models) and different uncertainty methods (eg, parametric and nonparametric bootstrapping) will be explored to facilitate investigation of the impact of various cost assumptions.

As a secondary cost objective, we will compare the cost and quality-adjusted life years (QALYs) between the two groups using the net benefit regression framework (see Table 3). QALY is a preference-based utility measure of HRQL, as perceived by the patient, that incorporates both length of life and quality of life into a single measure [137,138]. We aim to determine the incremental net benefit of interventions versus usual care. To estimate QALYs gained, we will convert SF-12v2 data collected to utility scores using a validated algorithm. We will also estimate the incremental cost per QALY gained. A cost-effectiveness acceptability curve (95% CI) will be used to characterize the uncertainty of our findings [139].

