### Controls for Bias

To limit sampling bias, a recruitment schedule randomly generated to ensure representation from each surgical group will be used. Contamination should not exist between groups as we will control who interacts with the SVN and intervention features. Those allocated to the intervention group will be asked not to share their tablets or demonstrate application features to any peers assigned to the control group. To evaluate cointervention, we will track participant receipt of any monitoring or recovery support-related interventions, outside of expected usual care up to 8 weeks postoperation. RAs responsible for outcome data collection will be separated from randomization procedures, will have no permitted access to IWRS, will not be involved in intervention delivery, and will be blinded to group allocation. An event adjudication committee responsible for adjudication of all clinical outcome data will be blinded to randomized allocation. The team has extensive experience with assiduous follow-up procedures to minimize losses to follow-up.

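### Recruitment is planned by surgery type, but surgery type is named neither in the primary model nor in the subgroup list, so no planned analysis shows the effect in cardiac and vascular patients separately

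*Protocol article*

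**What the plan says.** All references are to the protocol article.

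- **Recruitment.** Feasibility sets a target by surgical group: "Each site will target recruitment of 14 cardiac and 16 vascular patients during 3 weeks of recruitment". It runs over "five serial, parallel waves of approximately 30 patients per site", and "recruitment of 300 participants will be completed in 10 months’ time". Controls for Bias adds that "a recruitment schedule randomly generated to ensure representation from each surgical group will be used".
- **Reason for combining the groups.** The section on targeting seniors after cardiac and vascular surgery says that the factors behind poor recovery are shared by both groups, and aims at integrated care.
- **Allocation.** Randomization and Allocation describes random block sizes and names no stratification factor.
- **Primary model.** Primary Analyses specifies a linear mixed model with a contrast on movement pain and names no surgery-type term.
- **Subgroups.** "Two types of separate subgroup analyses are planned to determine the impact of gender-based pain expectations and patient sex on intervention effectiveness". Table 3 lists the same two.
- **Pooling.** Sample Size makes the combined analysis depend on the Canadian and UK samples being sufficiently alike. It sets no such condition for the two surgery types.

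**The concern.** Surgery type is recorded for every patient and used to steer recruitment. The case for one integrated program rests on the two populations being alike in what matters for recovery, and the trial could examine that directly. The stated analyses do not.

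The article's own background is mixed on the point. Chronic pain rates are called similar in range, but the pain sites differ (sternal and vein-harvest sites against the femoropopliteal tunnel). Surgical site infection is given as 4.4% after coronary bypass and 2.2% after vascular surgery.

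At stake is interpretation. A pooled difference could reflect a similar benefit in both groups or a benefit mainly in one, and a reader who follows the stated plan would not learn which.

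**Working it through.** **Inputs from the article.** 14:16 per wave per site, 5 waves, 2 sites; SD 20 on a 0–100 scale; two-sided alpha 0.05; 80% power; target difference 10 points; 256 patients with complete data; design effect 1.5 for the combined sample.

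**Assumption.** The cardiac–vascular difference in mean pain, D, is not given. I take D from 2 to 20 points.

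**1. The plan's own figures.**
- Per site: a t-test with d = 0.50 needs 63.8, so 64 per arm; 64/0.9 = 71.1, so 72 per arm. This agrees with the article.
- Combined: effective n per arm = 256/1.5/2 = 85.3. Detectable difference = 20 × 2.802 × √(2/85.3) = 8.58 points, d = 0.43. This agrees with the stated 8.6.

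**2. Planned mix.** 14 × 5 × 2 = 140 cardiac and 16 × 5 × 2 = 160 vascular, 300 in all. The cardiac share is p = 14/30 = 46.7%. Applied to 256 complete patients, this gives about 119.5 cardiac and 136.5 vascular.

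**3. Precision by surgery type, pooled over sites, design effect 1.** SE = 20 × √(4/n).

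| | n | SE | 95% half-width | Power for 10 points |
|---|---|---|---|---|
| Cardiac | 119.5 | 3.66 | 7.2 | 78% |
| Vascular | 136.5 | 3.42 | 6.7 | 83% |

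**4. Interaction (difference between the two effects).** SE = √(3.66² + 3.42²) = 5.01.
- Detectable at 80% power: 2.802 × 5.01 = 14.0 points.
- Power for a 10-point interaction: Φ(10/5.01 − 1.96) = 51%.
- With 300 less 10% (270 patients): 13.7 points and 54%.
- If the article's design effect of 1.5 were applied here too, half-widths and detectable differences would grow by √1.5 = 1.22, so 14.0 becomes about 17.2 points.

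**5. Precision gained by adding surgery type to the model.** R² = p(1 − p)D²/20² and SE ratio = √(1 − R²), with p(1 − p) = 0.249.

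| Assumed D | R² | Reduction in SE |
|---|---|---|
| 2 | 0.2% | 0.1% |
| 5 | 1.6% | 0.8% |
| 10 | 6.2% | 3.2% |
| 15 | 14.0% | 7.3% |
| 20 | 24.9% | 13.3% |

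At D = 10 the combined detectable difference would move from 8.58 to 8.31 points.

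**6. What pooling can hide (illustration only).** An effect of 10 points in cardiac and 0 in vascular patients averages to 10 × 14/30 = 4.7 points, well below the 8.6 that the combined sample is planned to detect. The article gives no evidence for this pattern.

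**The case against.** The strongest reply is that this is a condensed article. It names no covariates for the primary model at all, and covariate lists and stratification factors often sit in an analysis plan that is not shown. That stands in part. One can say that surgery type is not named in the primary model, but not that it enters no model. The cost regression, indeed, states that "the regression model will adjust for potential confounding variables", without listing them. The subgroup analyses are different: the text gives a count and names them. Table 3 is weaker support, because other sections refer to it for N-of-1 and quality-adjusted life-year analyses that it does not list.

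A second reply is that an interaction with 51% power for 10 points settles little. That is true of a significance test, but not of two estimates with intervals of about ±7 points.

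Several stronger readings are tempting, and the documents do not support them:

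- **A fixed quota.** The text gives a target, not a fixed number.
- **Chance imbalance biases the result.** With 72 per arm and allocation that ignores surgery type, the vascular share could differ between arms by about 16 percentage points (95% range). At D = 10 that is 1.6 points. But a site's 95% half-width is 1.96 × 20 × √(2/72) = 6.5 points, and this variation is already part of it. Randomization keeps the pooled estimate unbiased.
- **The sentence on administrative outcomes is wrong.** It says that "complex modeling for these outcomes will not be performed, as potential confounders are considered to be adjusted for in the design". It covers only chi-square tests of categorical outcomes, which are valid comparisons of randomized arms. Adjusting a different outcome, cost, does not contradict it.
- **The cost projection uses the recruitment mix.** Scalability promises a "projected model of total cost of 1-year SMArTVIEW patient throughput, based on site surgical volumes". Nothing there says that an unweighted trial average will be applied.
- **The trial cannot show the effect by type.** It can, since the data will exist. What is missing is a planned analysis.

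**Conclusion.** The point holds in a limited form. Both surgical groups are deliberately recruited and combined on a stated premise of similarity, and no stated analysis examines the effect by surgery type. No planned estimate is invalid because of this.

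The main loss is interpretive. Planned enrolment would support by-type estimates of about ±7 points, and that information is not planned for. This figure rests on SD 20, 256 complete patients, the 14:16 mix being achieved, and design effect 1.

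Precision is secondary. For assumed differences between types up to 10 points, adjustment shortens the standard error by about 3% or less; only from about 15 points does it exceed 7%. The documents give no figure that would place D in this range.

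**What to change.** 1. Name surgery type (cardiac or vascular) as a fixed effect in the primary mixed model.
2. Prespecify one allocation-by-surgery-type interaction on the primary outcome. Report the effect with its 95% CI in each type, together with the interaction estimate and its CI. Do not make the by-type results depend on a significant interaction, as Subgroup Analyses does for pain expectations: a 10-point interaction would fail that gate about half the time.

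The sentence on administrative outcomes and the cost projection need no change on this account.

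The cost is wording in the protocol and analysis plan, with no new data. The downside is one further imprecise estimate, with 80% power only for about 14 points with 256 patients. The report should say that a wide interval spanning zero does not show equal effects.

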### Data Analyses

#### Primary Analyses

Table 3 summarizes all data analyses. Using the intent-to-treat principle [128], all patients will be included in the final analysis and according to the group to which they were randomly allocated. Descriptive statistics will be used to describe sample characteristics using measures of central tendency and dispersion for continuous factors, and frequencies and proportions for categorical factors. A two-sided significance level of .05 will be used for all inferential analyses. Statistical methods used will depend on the type and distribution of data for the outcome variable under study. If outcome data meet requirements for parametric statistics, a linear mixed model [129] will be used to assess the effects of the intervention on the primary outcome. An a priori contrast of the weekly average worst score for the BPI-SF numeric rating scale *upon movement* (previous 24 hours) will be used to evaluate the primary endpoint of acute postop pain at 30 days postrandomization.

Linear mixed models, using an autoregressive [130] covariance structure—allowing for correlations between measurements to decline as they are further apart in time—will be used to evaluate within-patient variation in patient-reported outcomes over 12 months of follow-up. Linear mixed models are a flexible and powerful approach to the analysis of data with a complex variance structure, such as correlated data [129-131]. Unlike traditional repeated-measures designs, these models do not require complete data on each patient and have increased statistical power [132]. Nonlinear mixed models will be used in the following cases: (1) if continuous data violate assumptions of normality [132] and (2) for categorical secondary outcomes (eg, adverse event). Chi-square tests of association will be used to assess the association between categorical secondary outcomes identified in the administrative data and intervention. Given that the data is derived from an RCT, complex modeling for these outcomes will not be performed, as potential confounders are considered to be adjusted for in the design. Finally, we will examine patterns of missing data and determine demographic and/or clinical characteristics that are related to missing data at each time point, and the potential impact on the primary findings.

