##### Sample Size

Assuming a two-sided type I error (alpha) of .05 and a standard deviation of 20 points in BPI-SF numeric rating scale scores (range 0-100), a total of 128 participants (ie, 64 individuals in each group) are required to provide 80% power to detect a minimally important difference of 10 points. This difference represents a moderate effect size (Cohen’s d=0.50) [126]. Assuming a 10% loss to follow-up, 144 total patients (or 72 per group) is required. We will use this sample size for each site, to allow for site-specific analyses with equal and sufficient power. If there is sufficient homogeneity between the Canadian and UK samples, the combined sample (eg, 256 patients with complete data) would provide 80% power to detect a difference in pain intensity scores of 8.6 points (Cohen’s d=0.43), assuming a generous design effect [127] of 1.5 due to the clustering of participants within the site.

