**Primary outcome**				
	8-week worst postop pain intensity *upon movement* score in the past 24 hours	Intervention > control	Measured by Brief Pain Inventory-Short Form (BPI-SF^a^)	Linear mixed model or nonlinear mixed models (if assumptions of normality are violated)

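### A normality check on the observed outcomes chooses the primary model, and after a switch the effect measure need not be the 10-point mean difference used to size the trial

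*Protocol article*

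**What the plan says.** In the protocol article, Data Analyses, Primary Analyses, the primary model is conditional: "If outcome data meet requirements for parametric statistics, a linear mixed model" is to be used for the intervention effect. The next paragraph gives the alternative: "Nonlinear mixed models will be used in the following cases: (1) if continuous data violate assumptions of normality". The same sentence gives a second use for that class, "for categorical secondary outcomes (eg, adverse event").

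Table 3 carries the condition into the primary outcome row: "Linear mixed model or nonlinear mixed models (if assumptions of normality are violated"). The same entry stands against functional status, depressive symptoms, health service utilization cost and patient-level cost.

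Three other places bear on this:
- The Abstract gives a linear mixed model for the primary outcome and attaches no condition.
- Sample Size works in mean points. It takes "a standard deviation of 20 points in BPI-SF numeric rating scale scores (range 0-100") and asks for "80% power to detect a minimally important difference of 10 points".
- Cost-Effectiveness Analyses observes that ordinary least squares is in theory unbiased under skew, and treats other estimators as additional explorations.

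**The concern.** The rule is written out, so this is not a detail left to an unseen analysis plan. It has three faults.

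- The decision between two primary models is taken on the trial's own outcome data. The condition refers to the outcome data, whereas the normality assumption of a linear mixed model concerns its residuals and random effects.
- The trial is sized on a difference in means. If the replacement model works on another scale, the primary estimate is no longer in the units of the 10-point target.
- The article is not consistent with itself. The Abstract has no switch, and the cost section regards skewness as no obstacle to a linear model, yet Table 3 makes normality the trigger for the cost outcomes as well.

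At stake are the interpretability of the primary result and protection against choosing an analysis after seeing outcomes.

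**Working it through.** **1. The plan's own figures reproduce, and they rest on a difference in means.** Inputs from Sample Size: two-sided alpha 0.05, power 80%, SD 20, difference 10.
- n per arm = 2 × (1.960 + 0.842)² × 20² / 10² = 62.8, so 63. The t-distribution version gives 63.8, so 64 per arm, matching "a total of 128 participants (ie, 64 individuals in each group").
- With 10% loss: 64 / 0.90 = 71.1, so 72 per arm and 144 per site, as stated.
- Combined sample: 256 / 1.5 = 170.7 effective patients, or 85.3 per arm. Detectable difference = 2.802 × 20 × √(2 / 85.3) = 8.58, matching the stated 8.6.

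**2. How often would the switch fire?** The article names no test, threshold or expected mean, so these are assumptions: Shapiro-Wilk at 0.05 on within-arm residuals, scores bounded on 0-100 with SD 20, and 2,000 runs per cell. Four shapes were used: a continuous beta, the same beta rounded to steps of 10, the same beta rounded to the grid of a 14-day average, and a normal censored at 0. The table gives the range of rejection rates across shapes.

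| Assumed mean | 64 per arm | 128 per arm |
|---|---|---|
| 20 | 100% | 100% |
| 25 | 100% | 100% |
| 30 | 93.5-100% | 100% |
| 40 | 8-93% | 36-100% |
| 50 | 3-83% | 5-99.7% |

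A variant built the endpoint as a 14-day average of integer daily scores (between-patient SD 20, within-patient SD 15; 1,000 runs per cell). At latent means of 20, 30, 40 and 50 it rejected in 100%, 78%, 16% and 7% of runs with 64 per arm, and in 100%, 100%, 55% and 15% with 128 per arm.

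**3. Is the switch needed?** In the first set of simulations, a two-sample mean comparison with no switch had type I error of 0.038 to 0.061 across all shapes, means and both sample sizes. The Monte Carlo standard error is √(0.05 × 0.95 / 2000) = 0.005. Power for 10 points at 64 per arm was 0.783 to 0.811 for means of 25 to 50, the range over which power was evaluated.

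**4. What would the effect measure be after a switch?** A fixed 10-point reduction is not a fixed effect on other scales:

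| Control mean | Mean ratio | Logit difference |
|---|---|---|
| 20 | 10/20 = 0.50 | -0.81 |
| 30 | 20/30 = 0.67 | -0.54 |
| 40 | 30/40 = 0.75 | -0.44 |
| 50 | 40/50 = 0.80 | -0.41 |

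The logit column is ln[p/(1-p)] at the treated mean minus the same at the control mean, with p = mean/100. A comparison on a log-transformed score can even differ when means do not. With both means at 30 but SDs of 20 and 26, the mean difference is about 0 and the difference in mean log(1+x) is 0.26. That last example concerns a transformation of the data, not a log link on the mean.

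**The case against.** Several stronger readings are tempting, and the article does not support them.

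- *The switch is bound to fire, so the linear model would hardly ever be used.* This is not shown. A 100% rejection rate reflects a choice of low-mean or coarse shapes, and the figure falls to a few per cent at moderate means for some shapes. The endpoint is also an average of daily scores, which softens floor and rounding effects.
- *Nonlinear mixed models do not deal with non-normality at all.* In the strict sense, nonlinear describes the mean function. But the same sentence gives the class to categorical outcomes, so generalized linear mixed models were probably meant, and those can accommodate non-normal responses. That makes the word a matter for clarification.
- *The estimand changes.* No link is stated, and an identity link would keep the difference in points. What can be said is that the effect measure after a switch is not tied to the sizing. Distribution and link may properly sit in an analysis plan that is not shown, and their absence is not counted here.
- *The class is wrong for one-off 30-day events because a patient has no repeated measure.* The article specifies no patient random effect, and its sample-size text speaks of clustering within site. Table 3 also puts chronic postsurgical pain in a row with this class, and that outcome is assessed repeatedly from 3 to 12 months.
- *The simulation proves the switch useless.* It fitted neither the planned autoregressive mixed model nor any replacement. It shows only that a simple mean comparison is robust.

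An abstract also condenses, so its silence on the condition is weak evidence by itself. What stands after all this is the conditional rule, stated twice, and its poor fit with the sizing and with the cost section.

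**Conclusion.** The point holds for the rule itself. The article lets a normality check on observed outcomes choose the primary model and the models for four continuous secondary outcomes. It thereby loosens the link between the primary estimate and the 10-point difference that justifies 128 (144 with losses) patients per site.

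The practical exposure ranges from slight to near certain (about 3% to 100% in simulation), depending on the mean and shape of the scores, which the article does not give. Validity does not call for the switch, since size stayed near 5% and power near 80% without it. That conclusion assumes bounded scores with SD 20, the four shapes tried, and a two-sample comparison standing in for the repeated-measures contrast.

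This should be corrected before outcome data are seen. It does not make the trial's design or sample size wrong.

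**What to change.** In Primary Analyses and in Table 3, name the linear mixed model as the primary analysis whatever the distribution of the scores. Report the difference in mean points at the primary time point, with robust or bootstrap standard errors. Apply the same rule to the continuous secondary outcomes. Move any alternative model to a named sensitivity analysis that cannot replace the primary result. Where generalized linear mixed models are meant for categorical outcomes, use that term.

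The cost is a few lines of text. Sample size (128 and 144 per site), the 8.6-point detectable difference and data collection are unchanged.
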